#### Posttest Phase

The data will be recollected on all outcome measures during posttest phase 1, which is right after the intervention, and posttest phase 2, which will be after 8 weeks of the intervention (Figure 2).

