### Research Questions

The primary research question about suicidal ideation is as follows: What is the effect of suicide prevention programs (RAAHI and safeTALK) in reducing suicidal ideation among school-going adolescents in GB?

The secondary research question is as follows: What is the effect of suicide prevention programs (RAAHI and safeTALK) among school-going adolescents in GB on (1) perceived suicidal awareness; (2) perceived Social Support Questionnaire; (3) suicide literacy; (4) attitude toward seeking help related to suicidal ideation; (5) life attitude schedule; (6) depression, anxiety, and stress level; (7) adaptive coping strategies; and (8) self-efficacy.

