#### Intervention

The intervention phase consists of 2 workshops in which the students will be required to participate. The first workshop consists of 2 hours of RAAHI intervention which will provide them with general knowledge about suicide, risk factors, consequences, and preventive strategies; this will help participants improve their suicide literacy. Moreover, a booklet comprising different activities will also be provided to participants during the training. In addition, the second session will introduce the 4-hour safeTALK program, which seeks to increase people’s self-awareness and help-seeking behavior while reducing suicidal ideation. This is a culturally relevant program as it applies basic TALK steps and connects the person with suicidal thoughts with suicide first aid help and further community resources. Moreover, a pocket card containing the “suicide alert steps” will also be provided to the participants at the end of the training. In this study, the safeTALK workshops will be delivered to adolescents, approximately 30 students at a time. The researcher, along with a psychologist, will administer this training with the help of translated videos and material in Urdu, which is culturally appropriate and has been modified and adapted from LivingWorks.

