#### Depression, Anxiety, and Stress Level

The depression, anxiety, and stress levels will be assessed by the DASS-21 questionnaire, which was translated into Urdu, the national language of Pakistan, by Gillani et al [62], to assess the perceived stress levels and psychological well-being of the Pakistani population in Islamabad. Its internal consistency was assessed, revealing a Cronbach α of 0.94. DASS-21 will serve as a screening tool, evaluating stress, depression, and anxiety over the past week through 21 items, each consisting of a set of 7 questions. Responses on the Likert scale range from 0 to 3, where “never” corresponds to 0, “sometimes” to 1, “frequently” to 2, and “always” to 3. [63]. Depression, anxiety, and stress levels of participants will be assessed using predefined cutoff values as follows: depression score of less than 6, anxiety score of less than 5, and stress score of less than 9, in accordance with the DASS-21 guidelines [64].

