### Time Frame for Data Collection

Each participant will receive a short questionnaire at 3 points in time: pretest baseline data (T1), immediately after the intervention (T2), and 8 weeks after the intervention (T3). This self-filled questionnaire will collect data on suicidal ideation, level of suicide literacy, level of confidence, and openness to disclose suicidal ideas to others. The researcher will be responsible for checking for and verifying any missing data with participants, which will help to identify and correct errors in the datasets.

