### Strengths and Limitations

Because there is no standard intervention available for suicide prevention for adolescents in the Pakistani context, this research will assist in upscaling suicide prevention interventions tailored to the cultural and social context of GB among school-going adolescents in Pakistan. This study aims to bridge this gap by evaluating the effectiveness of suicide prevention programs specifically designed for Pakistani adolescents, thereby providing crucial data to inform national mental health strategies and policies. This study’s strong pre- and postintervention design enabled a clear evaluation of the program’s immediate effect on participants’ mental health. The use of established measurement instruments bolsters the dependability of our results.

However, due to time, budget, and logistical constraints, this feasibility study will only be conducted in 4 schools in GB, Pakistan, limiting potentially diverse implementation experiences and outcomes in rural or public-school settings. This may restrict the generalizability of the study findings. Moreover, using a quasi-experimental design without an appropriate control group can potentially undermine the internal validity of the study. Third, this study’s sample was limited to school-going adolescents, potentially restricting the generalizability of findings to out-of-school adolescents or other high-risk groups. In addition, the absence of a long-term follow-up limits our ability to determine the sustained impact of these interventions. However, reliance on self-reported data raises the possibility of response biases, particularly social desirability, which is significant given the prevailing mental health stigma in this area. Furthermore, while we acknowledge the potential influence of factors such as socioeconomic status, family support, and preexisting mental health issues, these were not fully controlled in our analysis. Future research should strive to include a broader range of variables to strengthen the study’s conclusions. Finally, it is important to note that the results of this investigation are specific to the studied context and may not be readily applicable to different cultural or geographic populations.

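### DASS-21 asks about the past week, so its reading right after the workshops (T2) cannot show an effect of the combined programme or support the claimed immediate mental-health effect

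*Protocol article*

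**What the plan says.** The Posttest Phase section sets two follow-up assessments and applies the full set of outcomes to both: "The data will be recollected on all outcome measures during posttest phase 1, which is right after the intervention", then again 8 weeks later. Time Frame for Data Collection gives the same timing, "immediately after the intervention (T2), and 8 weeks after the intervention (T3"), with baseline as T1.

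DASS-21 is an outcome. Item 6 of the secondary research question is "depression, anxiety, and stress level", and the outcome section describes the instrument as "evaluating stress, depression, and anxiety over the past week through 21 items". Nothing in the article exempts DASS-21 from T2 or changes its recall period there.

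On the programme itself, the Intervention section says: "The intervention phase consists of 2 workshops in which the students will be required to participate". RAAHI comes first and the 4-hour safeTALK workshop second. The interval between them is not given.

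Strengths and Limitations says that the pre-post design "enabled a clear evaluation of the program’s immediate effect on participants’ mental health". Study Design relies on the three time points to capture trends. Hypothesis 3 places the depression comparison at 8 weeks; the hypotheses fix no time point for anxiety or stress.

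Time Frame for Data Collection also says: "Each participant will receive a short questionnaire at 3 points in time". It then lists ideation, literacy, confidence and openness to disclose, and does not mention DASS-21.

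**The concern.** A questionnaire about the past week, filled in as a workshop ends, describes the week leading up to that moment. For DASS-21 at T2, that week precedes completion of the programme whose effect is to be measured. The plan nevertheless treats T2 as a posttest, and the Discussion credits the design with showing an immediate effect on mental health.

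The risk is a wrong conclusion on a stated secondary outcome. A flat T2 score could be read as no immediate effect, when the scale had no post-programme days to report on. A lower T2 score could be read as benefit, when it could come from retesting or from mood in the training room. With no control group, nothing in the design separates these explanations. A three-point trend that includes T2 would carry the same problem into the trend.

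**Working it through.** The plan gives no figure of its own to reproduce here. The check is arithmetic on the recall window.

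Inputs:
- Recall window: past week, 7 × 24 = 168 h (Depression, Anxiety, and Stress Level).
- T2: taken as the end of safeTALK (Posttest Phase; Time Frame for Data Collection).
- safeTALK: 4 h (Intervention; Intervention 2: safeTALK).
- RAAHI: the article gives two lengths. The Intervention section says "The first workshop consists of 2 hours of RAAHI intervention"; Table 1 and the RAAHI section give 3 h. Both are run below. The passages need reconciling, but the result hardly depends on which is used.
- Gap from the start of RAAHI to the start of safeTALK: not stated, so a range is shown as an assumption.

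**Share of the T2 window before safeTALK began**, at any gap: (168 − 4)/168 = 164/168 = 97.6%.

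**Share before the programme was complete**: 168/168 = 100% if T2 is at the end of safeTALK. If *right after* allowed a lag of a full day, it would be (168 − 24)/168 = 144/168 = 86%.

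**Share before RAAHI began.** Back to back: (168 − RAAHI hours − 4)/168. Otherwise: max(0, 168 − (24 × gap in days + 4))/168.

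| Gap | Calculation | Share before RAAHI |
|---|---|---|
| Back to back, RAAHI 2 h | 162/168 | 96.4% |
| Back to back, RAAHI 3 h | 161/168 | 95.8% |
| 1 day | 140/168 | 83% |
| 2 days | 116/168 | 69% |
| 3 days | 92/168 | 55% |
| 3.5 days | 80/168 | 48% |
| 5 days | 44/168 | 26% |
| 7 days | 168 − 172 < 0 | 0% |

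The share falls to one half when 24 × gap + 4 = 84, that is, at a gap of 80/24 = 3.3 days.

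**T3**: 8 weeks = 56 days. The recall week runs from day 49 to day 56 after the intervention, so it contains no pre-completion days. The T1 versus T3 comparison does not have this problem.

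**The case against.** The strongest reply is that the planned comparison is untouched. Hypothesis 3 tests depression at 8 weeks, and Data Analysis names suicidal awareness, literacy and help seeking for the mixed model, not DASS-21. This stands, and it limits the point to T2. It does not settle anxiety and stress, which have no time point in the hypotheses, and it does not remove the immediate-effect claim.

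The gap between workshops is also unknown. The first column of Table 1 refers to session or week, so weekly spacing cannot be excluded, and the two figures not reproduced in the text may give timing. This stands too. A reader might infer that T2 DASS-21 mostly describes days before any intervention; that holds only for gaps up to about 3 days. At longer gaps T2 could pick up some effect of RAAHI, but still not of the combined programme.

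*Immediate* in the Discussion may mean only short-term, since the next paragraph lists the lack of long-term follow-up as a limitation. That reading is possible. But the article uses *immediately* for T2, so the sentence invites the T2 reading and should be made exact.

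Finally, the list in Time Frame for Data Collection could mean that DASS-21 is not collected at T2. Read literally, it would remove DASS-21 from baseline and T3 as well, so it is better taken as a partial summary. If it did govern T2, the immediate claim would have no DASS-21 data behind it.

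Three further inferences are tempting and not supported:
- That the 8-week effect will be diluted by averaging T2 with T3. No section plans such an average.
- That the length of the battery degrades the other T2 answers. The article gives no completion time for T2 and nothing that shows such a loss.
- That T2 should be cut back to literacy, awareness and help-seeking. The article states a recall period only for DASS-21, and the cut would also remove the primary MSSI and several other scales without a reason.

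**Conclusion.** The point holds for DASS-21 at T2 and no further. With T2 at the end of safeTALK, the recall week lies wholly before programme completion and 97.6% of it before safeTALK began, whatever the gap between workshops. The share before RAAHI ranges from about 96% (back to back) to 0% (7 days apart). T2 DASS-21 therefore cannot show an effect of the combined programme and cannot support a claim of a clearly evaluated immediate mental-health effect.

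This rests on three readings: that respondents answer for the stated past week, that *right after* means the end of the second workshop, and that all outcome measures includes DASS-21. A one-day lag would still leave 86% of the window before completion. The T1 versus T3 comparison is sound on this point, and the documents give no ground for extending the criticism to the other T2 measures.

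**What to change.** - State that the DASS-21 depression, anxiety and stress effects are each estimated from T1 versus T3 only.
- Either omit DASS-21 at T2, or keep it and report it as a reading of the week before programme completion, excluded from any post-intervention or trend estimate of effect. If T2 values have already been collected, the second option applies. Any use of the scores for screening or referral is a separate matter that this analysis rule does not touch.
- Reword the sentence in Strengths and Limitations so that the mental-health conclusion rests on the 8-week assessment.
- Reconcile the questionnaire content listed in Time Frame for Data Collection with the statement in Posttest Phase that all outcome measures are repeated.
- State the interval between the two workshops, so that readers can judge what a T2 reading covers.
- Leave the other T2 measures, including the MSSI, as planned.

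The cost is a few lines of text. DASS-21 then contributes two time points rather than three to the effect analysis; what is given up is a value that could not be interpreted as an effect of the combined programme.

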**Figure 2 figure2:**
[figure not shown]
CONSORT (Consolidated Standards of Reporting Trials) diagram for participant flow.

### Data Collection Tools

A predesigned survey will be administered to individuals who express interest in participating in this study and willingly agree to provide the relevant information. The questionnaire consists of 3 sections. The first section will gather detailed demographic information and include eligibility questions, followed by the Modified Scale for Suicidal Ideation (MSSI) by Miller et al [43]. Its translated version is available as it was used in a study of suicide in Pakistan [50]. The second section includes questions about suicide literacy, confidence, and willingness to talk about suicide, followed by an attitude to seek help. In the last section, depression will be assessed using the Depression, Anxiety, and Stress Scale–21 Items (DASS-21), along with questions about the ability to adopt coping skills and self-efficacy.

### Study Outcomes

#### Suicidal Ideation

The level of suicide literacy among the participants will be measured through the MSSI by Miller et al [43], comprising 21 items. It was translated and used in Urdu by Bakht et al [51]. The MSSI has shown strong internal consistency, with a Cronbach α coefficient ranging from 0.87 to 0.94 [52]. The severity of suicidal ideation, as assessed by the MSSI total score, is categorized into 3 levels. A total score ranging from 0 to 8 indicates a low level of suicidal ideation. In contrast, a total score between 9 and 20 suggests a moderate level of suicidal ideation. These adolescents may experience more frequent or persistent thoughts of suicide, potentially accompanied by feelings of hopelessness or despair. Finally, a total score of 21 or higher reflects a severe level of suicidal ideation, indicating a significant risk of self-harm or suicide. Adolescents in this category may have intense and intrusive thoughts of ending their life, and immediate intervention and support are often necessary to ensure their safety. Severe suicidal ideation is indicated by a total MSSI score exceeding 20, coupled with an intense suicidal intention, represented by a score of more than 1 on item 7. In addition, an active desire to make an attempt is signaled by a score exceeding 1 on item 3, while a serious plan for suicide is indicated by a score of more than 1 on item 15.

#### Perceived Suicide Awareness

In total, 14 items of the Perceived Suicidal Awareness Scale from a previous suicide prevention study were used to evaluate perceived suicide awareness [2,48]. The original Perceived Suicidal Awareness Scale consists of 5 items assessing perceived knowledge about suicide and help-seeking resources, 3 items measuring willingness to discuss suicide and seek assistance, 5 items evaluating confidence in discussing suicide and obtaining help, and 1 item examining the intention to seek help. Responses were recorded on a 5-point scale, ranging from 0 (strongly disagree) to 4 (strongly agree). The scale was translated into Urdu and subsequently back translated into English. Any inconsistencies were identified, deliberated upon, and resolved. The finalized version was piloted with the target population. This scale has shown strong internal consistency, with a Cronbach α coefficient ranging from 0.87 to 0.94. Questions will be asked to determine the participant’s level of confidence while discussing issues regarding suicide. The questionnaire will use a Likert scale that will range from 1 to 3, where 1 will indicate “disagree,” whereas 3 will be read as “agree.” The scale was adopted from the studies by Kinchin et al [2] and Baggio et al [53]. The suicide skills confidence subscale (Cronbach α=0.84) assesses respondents’ confidence in working with clients with suicidal thoughts in regard to training, skills, comfort, and supervision. Possible scores range from 4 to 20, with higher scores indicating greater confidence. The questionnaire will also focus on determining the participants’ willingness to talk about suicide and suicidal ideation with others. To analyze the willingness, the statements will be assessed on a Likert scale ranging from 1 to 3.

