### Study Population

#### Inclusion Criteria

Both male and female adolescents enrolled in grades 9 and 10 who can comprehend English and Urdu will be included. In addition, adolescents and their parents must provide consent to participate in the study.

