### Conclusions

This study aims to evaluate the impact of RAAHI and safeTALK, culturally adapted suicide prevention programs, on adolescents in GB across 8 weeks. By measuring changes in suicidal thoughts, knowledge, and confidence, the research will inform evidence-based strategies for researchers, clinicians, and policymakers. These programs present a viable approach to combat the rising suicide rates, improve mental health, and promote positive attitudes within the community. However, long-term success requires addressing systemic challenges to ensure these interventions are integrated into wider public health systems.

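### Confidence is described through three incompatible components, one of them about work with clients, and the protocol does not say which one is the outcome

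*Protocol article*

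**What the plan says.** Everything here is in the protocol article. Under Study Outcomes, the Perceived Suicide Awareness section introduces a 14-item scale that includes "5 items evaluating confidence in discussing suicide and obtaining help", coded from 0 to 4. It reports that this scale was translated, back-translated and piloted in the target population.

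The section then turns to questions about how confident participants feel when discussing suicide, and says: "The questionnaire will use a Likert scale that will range from 1 to 3". Next it describes a suicide skills confidence subscale with an alpha of 0.84, which covers "confidence in working with clients with suicidal thoughts in regard to training, skills, comfort, and supervision". For that subscale it states: "Possible scores range from 4 to 20, with higher scores indicating greater confidence".

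The Inclusion Criteria define the respondents: "Both male and female adolescents enrolled in grades 9 and 10". The Introduction says the programme should give teenagers confidence to talk about suicidal feelings and encourage them to seek professional help.

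Confidence is treated as an outcome in several places. The Abstract lists it among the outcome measures. Pretest Phase, Data Collection Tools and Time Frame for Data Collection all include it. The closing Conclusions say what the study will do: "By measuring changes in suicidal thoughts, knowledge, and confidence".

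**The concern.** A subscale about clients and supervision describes the position of a professional helper. A school student has neither, so at least part of its content has no evident referent for these respondents. It is also not the confidence that the programme sets out to change.

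The section never says which of its three components yields the confidence score. A report could therefore present the client-work score as the trial's confidence result and still follow the text. A null change might then reflect content that students cannot relate to. A rise might reflect only that they had now attended a training. Neither would answer the question about confidence in talking about suicide or seeking help.

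Settling the response coding alone would not cure this. The client and supervision content would remain.

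**Working it through.** **1. Can the stated range be reproduced?** A sum of k items, each coded from a to b, runs from k×a to k×b. The item counts (5 and 14) and the codings (0–4 and 1–3) come from the Perceived Suicide Awareness section. The count of 4 is an assumption, one item for each of the four facets named. The 1–5 coding is also an assumption; the section does not state it.

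| Items | Coded 0–4 | Coded 1–3 | Coded 1–5 (assumed) |
|---|---|---|---|
| 4 | 0–16 | 4–12 | 4–20 |
| 5 | 0–20 | 5–15 | 5–25 |
| 14 | 0–56 | 14–42 | 14–70 |

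The stated 4–20 range cannot come from either stated coding, whatever the item count:

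- With 0–4 coding the minimum is k×0 = 0, never 4.
- With 1–3 coding a minimum of 4 requires k = 4, and the maximum is then 4×3 = 12, not 20.

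Four items coded 1–5 would give it (4×1 = 4, 4×5 = 20). So the subscale as described is a different instrument from both the five confidence items and the 1–3 questions.

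**2. Does the content fit?**

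| Component | Content as described | Fits students and the aim? |
|---|---|---|
| Five items of the 14-item scale | Discussing suicide, obtaining help | Yes |
| Questions coded 1–3 | Discussing suicide | Yes |
| Suicide skills subscale, 4–20 | Working with clients; training, skills, comfort, supervision | No, at least for clients and supervision |

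**3. Is there evidence that the subscale was adapted?** The article reports changes to other tools: minor adjustments to the social support questionnaire and one item removed from the suicide literacy scale. It reports none for this subscale. The translation and piloting statements come before the subscale is mentioned and concern the 14-item scale. The alpha of 0.84 is not tied to a student sample.

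**4. Can the consequence be sized?** Not from the document. An illustration needs inputs that are all assumed: four unit-variance items, inter-item correlation 0.5, a shift of 0.5 SD on each item that students can answer, and independent noise on the rest. The standardised change in the total would then be:

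- no empty items: 4×0.5 / √(4 + 12×0.5) = 2.0/√10 = 0.63
- one empty item: 3×0.5 / √(3 + 6×0.5 + 1) = 1.5/√7 = 0.57
- two empty items: 2×0.5 / √(2 + 2×0.5 + 2) = 1.0/√5 = 0.45

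This shows the direction of the risk only. It is not an estimate for this trial.

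**The case against.** The strongest reply is that the subscale may not be administered at all. The sentences about what will be asked refer to confidence in discussing suicide on a 1–3 format. The subscale sentence follows a statement about where the scale was adopted from, is in the present tense, and gives a range that the stated codings cannot produce. It could be a misplaced description of a source instrument. This reading is open, and the text does not exclude it. But the sentence stands in the outcome definition with its own score range and direction, so a reader cannot tell that it is only background.

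Second, a reader might infer that the trial's confidence outcome as a whole measures the wrong construct. The document does not support that. Two of the three components match the aim, and one of them belongs to a scale piloted in the target population.

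Third, a reader might infer that students cannot meaningfully answer the subscale. The items are not shown. Training, skills and comfort might be answerable after a workshop; only clients and supervision clearly lack a referent. Reliability and Validity of Tools also plans expert ratings of relevance and clarity, with low ratings prompting possible adjustment, together with pilot testing and Cronbach alpha. That could catch such items. However, the stated target is relevance in the Pakistani context and clarity of language, not whether a student has the role that the items presuppose.

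Finally, confidence is not a separate entry in the secondary research question, the null hypotheses or the outcomes named for modelling. It enters those only through suicide awareness. The primary question concerns suicidal ideation. This limits the consequences.

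**Conclusion.** The point holds in a limited form. Three components with incompatible scoring are offered for confidence, none is designated as the outcome, and one refers to professional work with clients that does not fit these respondents or the programme's aim. The firm parts are the described content, the stated population, and the arithmetic showing that 4–20 is unattainable under either stated coding. That the unsuitable score would be the one reported is a possibility, not a fact. No size of bias or dilution can be claimed.

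This concerns a secondary measure and leaves the primary outcome untouched. It should be corrected because the ambiguity allows a choice among scores after the data are seen.

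**What to change.** In the Perceived Suicide Awareness section:

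- Remove the suicide skills confidence subscale from the outcome set, with its 4–20 range and its alpha of 0.84.
- Define the confidence outcome as the sum of the five confidence items of the 14-item Perceived Suicidal Awareness Scale at T1, T2 and T3.
- State one coding. The 0–4 coding already described for that scale gives a total of 0–20.
- Delete the 1–3 format or reconcile it with that coding. If the forms already in use carry 1–3, say so and give the matching range for five items, 5–15, because finer responses cannot be recovered afterwards.

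The cost is a wording amendment and, if the subscale is in the questionnaire, a shorter form. No new data are needed, because Posttest Phase has all outcome measures collected again at both posttests. If collection is complete, the five-item score can still be fixed before analysis. The small loss is comparability with studies of professional helpers that used the subscale.
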